Zinc bioavailability from a mixed or vegetarian diet based on refined cereal grains is estimated to be 26–34%, whereas 18–26% is absorbed from an unrefined cereal-based diet [18]. The actual amount of absorbed zinc not only depends on the zinc content of the consumed diet but is highly affected by its intestinal zinc bio-accessibility and bio-availability [18]. The inhibitory effect of phytate on zinc absorption is concentration-dependent and has shown to be more important than the phytate content of the product itself [19]. Fermentation theoretically results in higher zinc bioavailability if a significant reduction of phytate is achieved.

Food fortification with zinc appears as an attractive public health strategy, with numerous programs initiated in developing countries as a cost-effective way to combat zinc deficiency [1, 12]. Systematic reviews evaluating zinc fortification indicate significant improvements in plasma zinc concentration, reduced prevalence of zinc deficiency, increased child weight, and enhanced short-term auditory memory. However, data for adolescents, pregnant women, and lactating women are limited [20]. Biofortified zinc flour have also shown mixed effects [21].

The aim of this randomized controlled trial (RCT) is to assess the effect of fermented and unfermented wheat flour flatbread from agronomically zinc biofortified and post-harvest fortified wheat flour when compared to conventional low-zinc wheat flour flatbread and its impact on health including zinc status, anthropometric outcomes, risk of T2DM and morbidity on adolescent and adult females. In Pakistan, common naan is a type of flatbread, is typically made from fermented maida (all-purpose low extraction) wheat flour, characterized by refined flour with minimal bran and germ. However, in most households, the community usually uses unfermented whole wheat flour flatbread. Wheat samples from various sites across Pakistan were tested, with zinc levels ranging from 20-50mg/kg. The trial chose two wheat varieties: conventional low zinc (20-25mg/kg) and high zinc content which is agronomically biofortified (>35mg/kg) which was grown under collaborator supervision at the study site.

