**Fig 2 pone.0304462.g002:**
[figure not shown]
Study groups.

Group 1: will receive fermented high zinc agronomically biofortified wheat (>35mg/kg) flour flatbread.Group 2: will receive unfermented high zinc agronomically biofortified wheat (>35mg/kg) flour flatbread.Group 3: will receive fortified (post-harvest) whole wheat (80mg/kg) flour flatbread.Group 4: will receive low zinc conventional whole (20–25 mg/kg) wheat flour flatbread.

The intervention duration will be six months, and participants will be provided with the respective ‘flatbread’ with a vegetable curry or pulse (*daal*) meal once a day for six days a week for six months This meal would be distributed at schools/colleges or community spaces during break or after the school is over.

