### Sample size and sampling strategy

#### Sample size calculation

The study sample size was calculated based on an individually randomized four arm design on the primary outcomes of mean serum zinc levels and HbA1c. The mean HbA1c taken was 5.62% (SD 1.96) [33] and mean serum zinc was 79.5 μg/dL (SD 35.9) according to NNS-2018 [1]. The sample size was determined with a power of 0.8 and alpha of 0.05 to detect a difference of at least 0.12 effect size in the mean serum zinc levels between groups and to detect a 0.2 effect size in the mean HbA1c levels with a dropout rate of 10%. The sample size calculated was 250 participants in each group, with 210 adolescents (aged 10–18 years) and 40 adult women (aged 20–40 years). Hence, a total of 1000 participants would be randomly allocated to each of the groups in a 1:1:1:1 ratio.

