### Trial analysis

This trial will adhere to CONSORT guidelines for randomized trials, with primary analysis on an intention-to-treat basis [22]. Both primary and secondary data will be analyzed following the same principle. Descriptive statistics will include mean and standard deviation for symmetrically distributed continuous variables, median and interquartile range for asymmetrically distributed ones, and frequency with percentages for categorical data. Associations between dependent and independent categorical variables will be accessed using chi-square test, while one-ANOVA will be used to assess difference in continuous outcomes by intervention groups. Significant association further assessed by post-hoc test adjusting for multiple comparisons. Multivariate analysis will be performed using mixed effect linear or logistic regression to assess the impact of intervention over time by including time and group interaction. The time and intervention group will be treated as fixed effect while students included in the model as random intercept. The potential confounding factors that are imbalance at baseline will also be included as fixed effect in the model. The minimal adequate model for regression will be computed using the backward procedure. Statistical Significance will be set at p-value of <0.05. To assess the robustness of the findings, a sensitivity analysis will be conducted, and a dose-response relation will also be assessed.

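### The ANOVA route reaches the three control comparisons only through a four-arm omnibus test and an unnamed post-hoc correction; planned contrasts against Group 4 would match the objective at somewhat better power

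*Protocol article*

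**What the plan says.** The Introduction frames the aim as the effect of the fermented, unfermented and post-harvest fortified products "when compared to conventional low-zinc wheat flour flatbread", and the Objectives section repeats this. That makes three comparisons, each against Group 4.

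The Trial analysis section states that "one-ANOVA will be used to assess difference in continuous outcomes by intervention groups", with a chi-square test for categorical data. It continues: "Significant association further assessed by post-hoc test adjusting for multiple comparisons". It names no procedure and does not say whether the correction covers the three control contrasts or all six pairs. The threshold is general: "Statistical Significance will be set at p-value of <0.05".

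The same section then plans a mixed linear or logistic regression with a time-by-group interaction. This step does not depend on the ANOVA result. The section lists no contrasts for the model and does not say which of the two analyses is primary. It also says that the regression will be reduced by a backward procedure, and it does not exempt group or the interaction.

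The Discussion adds two further questions: biofortified against fortified wheat, and the added effect of fermentation.

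**The concern.** An omnibus F test asks whether any of four means differ. The objective asks whether each of three products beats control. When the second question may be asked only after the first is answered yes, a control contrast that would be significant on its own adjusted test can be lost. The F gate is not needed to protect the three control contrasts, because Dunnett's many-to-one procedure already controls the familywise error for them.

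The loss from a gate depends on the pattern of means. It is smallest when one arm alone works and larger when the means are graded. The protocol's zinc contents suggest grading: control at 20–25 mg/kg, biofortified above 35, and a third group that "will receive fortified (post-harvest) whole wheat (80mg/kg) flour flatbread". At stake is some power for the comparisons that the trial was set up to make, and clarity about which result answers the objective.

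**Working it through.** **Inputs from the Sample size calculation section.** "The sample size was determined with a power of 0.8 and alpha of 0.05". For zinc, "to detect a difference of at least 0.12 effect size in the mean serum zinc levels between groups"; for HbA1c, "to detect a 0.2 effect size in the mean HbA1c levels with a dropout rate of 10" per cent. There are 250 per group, so 250 × 0.9 = 225 evaluable. The type of effect size and the sidedness are not stated.

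**The plan's own figure.** Read as Cohen's f with four groups (noncentral F, λ = N·f²), f = 0.12 needs 191 per group for 80% power, and 191 / 0.9 rounds up to 213. Inflating by multiplication gives 191 × 1.1 = 210. This is close to the 210 adolescents per group but does not reproduce 250. Read as Cohen's d, 0.12 would need 1,091 per group. I therefore take 0.12 as f. The mismatch with 250 is a separate matter and does not bear on this point.

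**Assumed pattern.** On flour zinc, the biofortified increment relative to the fortified one is (35 − 22.5) / (80 − 22.5) = 0.22. I use 0.2. Because ">35" is a floor, the ratio could be higher: wheat sampled across Pakistan reached 50 mg/kg, and (50 − 22.5) / 57.5 = 0.48. I therefore also show 0.4.

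**Converting f to a difference.** Let fortified lie d SD above control and both biofortified arms 0.2d above it. The grand mean is 1.4d / 4 = 0.35d. Then f² = d² × (2 × 0.15² + 0.65² + 0.35²) / 4 = 0.1475d², so f = 0.384d. For f = 0.12, d = 0.31. For d = 0.25, f = 0.096.

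**Power for fortified versus control.** Simulation with 400,000 trials per scenario, 225 per arm, pooled variance, two-sided tests, F gate at 0.05. Critical values: Dunnett 2.35, Tukey 2.57, Bonferroni over six pairs 2.64.

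| Scenario | Direct Dunnett | Gate + Dunnett | Gate + Tukey | Gate + Bonferroni-6 |
|---|---|---|---|---|
| f = 0.12 (d = 0.31), ratio 0.2 | 83% | 80% | 76% | 74% |
| d = 0.30, ratio 0.2 | 80% | 76% | 72% | 70% |
| d = 0.25, ratio 0.2 | 62% | 57% | 52% | 50% |
| d = 0.25, ratio 0.4 | 62% | 55% | 51% | 49% |
| f = 0.12 (d = 0.277), one effective arm | 72% | 71% | 64% | 61% |

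**Separating the gate from the correction.** At f = 0.12 and ratio 0.2, ungated power is 83% with Dunnett, 77% with Tukey and 75% with Bonferroni-6. The gate alone therefore costs about 3 points with Dunnett, and 1 or less with Tukey or Bonferroni-6. At d = 0.25 it costs 5 points with Dunnett at ratio 0.2 and 7 at ratio 0.4. At d = 0.25 and ratio 0.2, ungated against gated power is 53.2% against 51.8% for Tukey and 50.4% against 49.7% for Bonferroni-6. Most of the fall from direct Dunnett to the gated all-pairs methods thus comes from correcting for six pairs rather than three.

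**HbA1c.** At f = 0.2 with one effective arm, power is 99.4% direct and 98.8–99.4% gated, a cost of 0 to 0.6 points.

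**The case against.** The strongest reply is that the plan does not make control comparisons depend wholly on the F test. The mixed model follows in the same section, is not gated, and with group as a fixed effect can estimate each arm's change against a reference. A reader might infer that control comparisons are permitted only after a significant ANOVA, so that a real benefit would go unreported. The document does not support that. What remains is that the model is not designated primary, no contrasts are named for it, and backward elimination without an exemption could drop a non-significant interaction, which would act as another omnibus gate.

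Second, the post-hoc method is unnamed, Dunnett would satisfy the wording, and naming it is commonly left to the analysis plan. This stands. A reader might take a fixed loss, such as 3 to 10 points, as a property of the plan. The losses of 7 to 9 points at the design effect (83% to 76% or 74%) hold only if an all-pairs method is chosen.

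Third, the graded pattern assumes that response follows flour zinc, while the Introduction says that absorption depends strongly on bio-accessibility and bioavailability. This also stands, so the pattern is an assumption. With one effective arm, the gate costs only about 1.6 points with Dunnett.

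Fourth, ANOVA with adjusted post-hoc tests is a valid four-arm analysis that fits the apparent sizing basis, and an all-pairs correction covers the active-arm comparisons in the Discussion. It would therefore be wrong to say that the planned route gains no error control. The narrower statement holds: for the three control contrasts, the F gate adds nothing that Dunnett does not already give.

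**Conclusion.** The point holds in a limited form. The ANOVA route puts an omnibus question ahead of the three comparisons that make up the objective, and the document does not say that the ungated mixed model is the analysis that answers them. For serum zinc at the stated effect, the gate costs about 3 points of power for fortified versus control if the post-hoc test is Dunnett (83% to 80%), rising to 5–7 points at a smaller effect of 0.25 SD. With an all-pairs correction the total loss is about 7 to 9 points, of which the gate accounts for 1 or less. For HbA1c at 0.2 the loss is negligible.

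These figures assume that the effect sizes are Cohen's f, tests are two-sided, variances are equal, dropout is 10% in every arm, adolescents and adults are pooled, each person contributes one endline value, and the biofortified effect is 0.2 of the fortified one (0.4 as a variant). The planned analysis is not invalid. This is an inexpensive improvement that aligns the analysis with the objective.

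**What to change.** In the Trial analysis section:

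- State that the primary comparison for each outcome is three planned contrasts, Groups 1, 2 and 3 each against Group 4, from the adjusted mixed model, with Dunnett-adjusted p-values and confidence intervals.
- Remove the omnibus test as a condition for these contrasts. The ANOVA may stay as a descriptive result.
- Exempt group, and its interaction with time, from backward elimination.
- Name biofortified versus fortified and fermented versus unfermented as secondary contrasts, with estimates, intervals and their own multiplicity adjustment.
- For the lipid profile, which is measured only at endline and so has no change over time to model, take the same three contrasts from an endline model.

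The cost is analysis wording only; no data collection or sample size changes. The downside is that the active-versus-active comparisons leave the primary error-controlled family, which should be stated openly because the Discussion presents them as a feature of the trial.

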### Baseline, midline, and endline data collection

Participants will undergo assessments at baseline and endline, where we will gather data on socio-demographic factors, dietary intake via 24-hour dietary recall, anthropometric measurements (weight, height, MUAC, waist circumference), blood pressure measurements, and blood samples will be collected for biochemical analysis, including serum zinc levels, FBS, HbA1C, and insulin at both time points. Lipid profile and RBC membrane fatty acids will be assessed only at the endline. At midline, we will conduct 24-hour dietary recalls, measure serum zinc and HbA1C for a subset from each group. The data for morbidity (diarrhea and ARI) will be collected fortnightly for the entire duration of the intervention.

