#### Morbidity

Incidence and duration of diarrheal episodes and respiratory tract infections will be recorded every two weeks throughout the study.

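### For diarrhoea and ARI, listed only as on-treatment records, the planned time-by-group interaction tests whether the arm difference changes, not whether arms differ; the morbidity effect measure should be named in advance

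*Protocol article*

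**What the plan says.** All points are from the protocol article.

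- **Outcome.** The Introduction includes morbidity in the trial's aim, and Outcomes lists diarrhoea and ARI as secondary.
- **Recording.** Under Baseline, midline, and endline data collection: "The data for morbidity (diarrhea and ARI) will be collected fortnightly for the entire duration of the intervention". Under Morbidity: "Incidence and duration of diarrheal episodes and respiratory tract infections will be recorded every two weeks throughout the study". The list of baseline measurements includes serum zinc and HbA1c but not morbidity. The intervention section gives the length: "The intervention duration will be six months".
- **Model.** Trial analysis plans a "mixed effect linear or logistic regression to assess the impact of intervention over time by including time and group interaction", and adds: "The time and intervention group will be treated as fixed effect while students included in the model as random intercept". A backward procedure then reduces the model.
- **Other comparisons of arms.** The same section says "one-ANOVA will be used to assess difference in continuous outcomes by intervention groups", with adjusted post-hoc tests, and "Associations between dependent and independent categorical variables will be accessed using chi-square test".

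The section is generic. It does not say which term is the effect measure for morbidity, and it makes no exception for outcomes without a pre-intervention value.

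**The concern.** A time-by-group interaction measures a treatment effect when one of the time points precedes treatment, because the arms are then alike in expectation at that point and any divergence is due to treatment. If every record is made on treatment, a benefit that is already present and stays constant produces no divergence. The interaction then answers a different question: does the gap between arms widen or narrow?

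The risk is one of interpretation. If the interaction p-value is read as the test of impact on morbidity, a steady reduction in diarrhoea or ARI could be reported as no impact over time. Conversely, a significant interaction could come from arms crossing over the season with no average benefit. The group coefficient does not settle the matter. With the interaction in the model it is the arm difference at whichever time is coded as the reference, and the protocol does not state that coding.

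**Working it through.** **1. The model.** For participant *i* in arm *g* at round *t*:

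logit P(ill) = α + u_i + βt + γ_g + δ_g·t

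- *Outcome with a baseline (serum zinc, linear version, t = 0 before treatment, t = 1 at endline).* δ_g = (endline difference from control) − (baseline difference from control), which is the treatment effect.
- *Outcome with on-treatment rounds only.* A constant benefit with odds ratio OR means γ_g = log(OR) and δ_g = 0. The null δ_g = 0 is therefore true, and the test rejects with probability α = 0.05 whatever the size of OR. γ_g is the arm difference at t = 0: the first fortnight if time starts there, mid-follow-up if time is centred.

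**2. Inputs from the protocol.** Four arms, 250 per arm, 10% dropout: 250 × 0.9 = 225 evaluable. Six months is about 26 weeks, and 26 / 2 = 13 fortnightly rounds. The protocol gives no power figure for morbidity. Its only size figure, 250 per arm, is reproduced if the 0.12 for serum zinc is read as 12% of the mean: 0.12 × 79.5 = 9.54; n = 2 × (1.960 + 0.842)² × 35.9² / 9.54² ≈ 223; 223 / 0.9 ≈ 248.

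**3. Assumptions not in the protocol.** Control risk 5% or 10% per fortnight, participant SD 1 on the logit scale, the same OR in all three zinc arms, linear time.

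**4. Rejection rates (%) under a constant benefit.** 400 simulated trials per row, two-sided 0.05, 3-df tests. The two regression tests use logistic regression with participant-clustered robust Wald statistics as a stand-in for the mixed model.

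| Control risk | OR | Time × group | Group, all rounds | Chi-square, ever ill | ANOVA, ill fortnights |
|---|---|---|---|---|---|
| 5% | 0.8 | 8.25 | 28.00 | 19.50 | 28.25 |
| 5% | 0.7 | 3.00 | 66.75 | 48.75 | 66.50 |
| 5% | 0.6 | 7.00 | 91.50 | 77.75 | 91.50 |
| 10% | 0.8 | 3.50 | 38.25 | 21.25 | 38.75 |
| 10% | 0.7 | 3.50 | 81.75 | 46.50 | 82.25 |
| 10% | 0.6 | 4.25 | 97.50 | 81.75 | 97.75 |

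Mean of the interaction column: (8.25 + 3.00 + 7.00 + 3.50 + 3.50 + 4.25) / 6 = 4.9%. The Monte Carlo standard error of one entry near 5% is √(0.05 × 0.95 / 400) = 1.1 points. The 8.25 is therefore a high draw, but the mean agrees with step 1. With no effect (OR 1) the interaction rejected in 5.25% and 4.75% of runs.

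**5. Cross-check with the random-intercept model itself.** Likelihood-ratio tests, 360 trials per scenario, time starting at the first fortnight:

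| Control risk | Effect | Time × group | Group, all rounds | Group term with interaction kept |
|---|---|---|---|---|
| 10% | OR 0.70, constant | 6% | 83% | 52% |
| 5% | OR 0.60, constant | 4% | 91% | 55% |
| 5% | OR 0.70, constant | 5% | 63% | 33% |
| 10% | OR 0.75, constant | 5% | 64% | 33% |
| 10% | OR 0.70 from one month on | 15% | 63% | 14% |

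A one-month delay gives the interaction some power, but far less than the group effect across all rounds.

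**The case against.** The strongest reply is that the interaction is one coefficient, not the trial's morbidity test. A reader might infer that the plan would miss a steady morbidity benefit about 95% of the time. The documents do not support that:

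- **ANOVA by arm is planned.** Applied to each participant's number of ill fortnights, it matches the group effect across all rounds in every row of the first table. The gap between the two regression tests is therefore not a loss of power for the plan as a whole.
- **Chi-square by arm is planned.** It also compares arms directly, with 20% to 82% power in the same scenarios.
- **Backward selection could remove a null interaction**, leaving group plus time, which is close to the remedy proposed here.
- **The 95% is simply 1 − α**, and holds only for an effect that is constant from the first round. Nor can the interaction model be said to be unable to detect such an effect, since its group term found one in 33% to 55% of runs when time started at the first fortnight.

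A reader might also take "Both primary and secondary data will be analyzed following the same principle" as assigning the interaction model to morbidity. That sentence directly follows the commitment to intention-to-treat, and this is the principle it means.

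Finally, this is a journal article. The statistical analysis plan is not shown and may name the morbidity effect measure. The SPIRIT schedule is also not visible, so a baseline morbidity record outside the text cannot be excluded.

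These replies narrow the point but do not remove it. The only stated model suited to repeated records targets the wrong contrast for this outcome. ANOVA recovers the power only on a per-participant summary that the article does not define for morbidity. Chi-square on ever ill discards the repeat episodes and durations that are recorded. If backward selection decides whether the interaction stays, it also decides what the group coefficient means: an average over follow-up if it is dropped, a difference at one reference time if it is kept.

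**Conclusion.** The point holds in limited form. For diarrhoea and ARI, as the text describes their collection, the time-by-group interaction tests change in the arm difference. Under a benefit constant on the logit scale it rejects at about 5%. That result follows from the model and does not depend on the assumed morbidity rates. The comparison powers do depend on them: 28% to 98% for a group effect across all rounds, over control risks of 5% to 10% and odds ratios of 0.8 to 0.6.

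The defect is that the stated impact model does not identify the morbidity effect, and a data-driven step could determine it. It concerns secondary outcomes that are named in the trial's aim. It does not touch serum zinc or HbA1c, where the interaction is the appropriate term. It is worth correcting because the correction is nearly free.

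**What to change.** Add to Trial analysis, before unblinding, wording such as:

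> For diarrhoea, ARI and any other outcome recorded only during the intervention, the effect measure is the contrast of each zinc flour with the low-zinc control, averaged over follow-up. It will be estimated as a rate ratio from a negative binomial or Poisson model of episodes (and of days ill) per participant, with log fortnights observed as offset. Backward selection will not determine this effect measure. The group-by-time term will be reported only to describe when any effect appears.

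The fortnightly mixed logistic model with group and fortnight as fixed effects and no interaction is an acceptable alternative, giving an odds ratio rather than a rate ratio. One of the two should be chosen in advance. If the statistical analysis plan already does this, a cross-reference is enough.

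The cost is one or two sentences, with no new data, participants or procedures. The downside is that the morbidity model differs from the biomarker model.

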#### Randomization and allocation concealment

Individuals will be randomly assigned in the four groups (red, blue, green, and black) through a computer-generated random number list. A statistician will assign the individuals into four groups by a computer-generated list and would then assign color codes (red, blue, green, black) without knowing which color belongs to which group. This randomization will be stratified on gender and age (10–13 years, 14-19years, 20–40 years old) and adjusted for serum zinc, BMI, zinc deficiency and HbA1C.

An independent consultant from an international University (University of Sydney) would be responsible for assigning the three intervention and control groups to each color group and will not be involved in the trial, including recruitment, implementation, or evaluation. The consultant would be responsible for generating and safeguarding the code and would be the only person communicating with the flour mill (Shoaib Corporation) and nutrition laboratory to ensure that the correct flour is being milled and packed in the right color bag for each batch. The consultant will break the code when the final data is collected and analyzed.

This flour mill site (Saleh Pat) is located about 500km from the trial site and the flour would be transported fortnightly to the field site. Shoaib Corporation has set up a separate local mill (chakki) for the study and has the warehouse where the two different varieties of wheat are being stored. They would be responsible to mill, fortify (ZnO - 80mg/kg) and pack high zinc, fortified, and low zinc wheat/flour in 40kgs polypropylene sacks, corresponding to a specific color. To ensure accuracy, fortnightly samples of color-coded products will be sent to the laboratory and the results will be shared with the consultant for confirmation.

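### The regression takes covariates from observed baseline imbalance and is then cut backward with no term protected, so the model is not known in advance, design factors tend to be lost, and the treatment term itself could be removed

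*Protocol article*

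**What the plan says.** All of this stands in the protocol article, mostly under Trial analysis.

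- **The model.** "Multivariate analysis will be performed using mixed effect linear or logistic regression to assess the impact of intervention over time", with a time-by-group interaction. On its terms: "The time and intervention group will be treated as fixed effect while students included in the model as random intercept".
- **How covariates enter.** "The potential confounding factors that are imbalance at baseline will also be included as fixed effect in the model". The article gives no list of candidates and no criterion for imbalance.
- **How the model is reduced.** "The minimal adequate model for regression will be computed using the backward procedure". There is no retention threshold, and nothing says that group, time or their interaction must stay.
- **The parallel analysis.** "one-ANOVA will be used to assess difference in continuous outcomes by intervention groups", with chi-square tests for categorical variables and adjusted post-hoc comparisons. These involve no model selection. The section does not say whether they or the regression are primary.

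Two other sections matter. Randomization and allocation concealment stratifies on gender and three age bands and says the randomisation is also "adjusted for serum zinc, BMI, zinc deficiency and HbA1C". The section on baseline, midline and endline data collection measures the lipid profile (a primary outcome) and the red-cell fatty acids at endline only.

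**The concern.** In a randomised trial, baseline imbalance is a chance event. Choosing covariates by it selects variables without regard to whether they predict the outcome. Factors that the randomisation has balanced will seldom look imbalanced, so the rule tends to leave out the variables the design treated as important.

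The backward step adds a second data-driven choice. The sentence refers to the regression as a whole, whose named terms are group, time and group-by-time. Read literally, it lets the procedure delete the interaction, which is the treatment effect in a repeated-measures model, or the group term for an outcome measured once.

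Both rules are stated in the text. An analysis plan that follows the protocol inherits them, so this is not detail left for later.

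**Working it through.** **1. The plan's own figure.** The article states 250 per arm, using "The sample size was determined with a power of 0.8 and alpha of 0.05", and aims "to detect a difference of at least 0.12 effect size in the mean serum zinc levels between groups". Inputs are mean zinc 79.5, SD 35.9 and 10% dropout; a two-sided test is assumed. Reading 0.12 as 12% of the mean:

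- difference = 0.12 × 79.5 = 9.54; 9.54 / 35.9 = 0.266 SD
- n = 2 × (1.960 + 0.842)² / 0.266² ≈ 222.3, so 223 per arm
- 223 / 0.90 = 247.8, so 248, close to the stated 250

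A standardised difference of 0.12 would need 1,091 per arm (1,213 with dropout). ANOVA f = 0.12 over four arms would need 191 (213 with dropout). So the planned zinc effect is about 0.27 SD. The checks below use 250 × 0.90 = 225 completers per arm.

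**2. Treatment kept in, covariates selected.** Simulated endline outcome, four arms, 12 candidate baseline variables of which 4 are prognostic, imbalance at p<0.05 followed by backward elimination at p<0.05. There were 6,000 null runs and 3,000 runs with 0.2 SD in one arm. None of these settings is in the article.

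| | R² 0.10 | R² 0.40 |
|---|---|---|
| Global type I error, article's rule | 0.052 | 0.044 |
| Mean estimate (true 0.20), article's rule | 0.201 | 0.198 |
| Power, one arm v control, article's rule | 56% | 56% |
| Power, pre-specified prognostic covariates | 61% | 77% |

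Analytic check: SE = √(2(1−R²)/225), which is 0.0943 unadjusted, 0.0894 at R² 0.10 and 0.0730 at R² 0.40. Power = Φ(0.2/SE − 1.96) is 56%, 61% and 78%, in line with the simulation.

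The loss comes from the imbalance rule. Backward elimination from the full candidate list, with treatment kept in, gave the same 61% and 77%.

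**3. The group-by-time estimate in the linear mixed model.** Twelve fits per scenario. With complete baseline and endline data, the estimate was the same for every set of main-effect covariates (difference about 1e-14) and its standard error stayed at 0.080. With a one-third midline sample and 10% missing endline data, the estimate moved by at most 0.010 SD.

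**4. Treatment terms open to elimination.**

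- Endline outcome, set-up of step 2: the mean retained effect was 0.238 (R² 0.10) and 0.236 (R² 0.40) against a true 0.20. 0.238/0.20 = 1.19 and 0.236/0.20 = 1.18, so 18 to 19% too large.
- Group-by-time term kept only if its 3-df test is significant, all three active arms differing from control, change variance 2(1−ρ)/225 per arm:

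| | ρ = 0.3 | ρ = 0.5 | ρ = 0.7 |
|---|---|---|---|
| 0.27 SD: retained | 68% | 84% | 97% |
| 0.27 SD: overstated by | 17% | 8% | 1% |
| 0.20 SD: retained | 43% | 57% | 81% |
| 0.20 SD: overstated by | 38% | 24% | 9% |

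- If the interaction is dropped, the group effect averages visits with and without an effect. With two complete visits its expectation is (0 + d)/2. In the fits of step 3 it was 0.118 against an interaction estimate of 0.192, and 0.104 against 0.170 with the midline sample and missing data.

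**The case against.** The strongest defence is that the backward step is meant only for the confounders. The section first fixes time and group as model terms, then brings in the confounders, and only then mentions the reduction. That reading is at least as natural as the literal one, and under it step 2 shows no inflation. This stands, and it limits the point: distortion of the treatment effect is conditional on how the sentence is applied. It does not remove the point, because the text never says which reading holds.

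Several stronger conclusions are tempting but not supported:

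- **That covariate selection by itself makes p-values invalid and effects too large.** With treatment kept in, the test was at or slightly below its nominal level and the estimate was unbiased.
- **That effects would be overstated by half or more.** This needs a true effect of 0.12 SD, where the step 4 calculation gives 46 to 93%. The stated sample size reproduces at about 0.27 SD.
- **That the overstatement shows a fault of covariate selection.** It is the ordinary result of reporting an effect only when it is significant.
- **That a spurious imbalance is 40% likely.** 1 − 0.95¹⁰ = 0.40 assumes ten independent tests at 5%. The article states no test, threshold or number of variables.
- **That the baseline value or the strata would be dropped.** In the repeated-measures model, baseline is a response row and not a removable covariate. The strata enter only if imbalanced, so the problem is that they are not put in.
- **That null outcomes would have no result at all.** Descriptive summaries, ANOVA and chi-square tests are also planned. They do not settle the matter, because the section does not say which analysis is primary.

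**Conclusion.** The point holds in a limited form. The article fixes a data-driven regression model when the relevant factors were known beforehand.

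- **Certain:** the final model for each outcome cannot be stated in advance and may differ between outcomes.
- **Likely, with size depending on assumptions:** lost precision, illustrated by 56% power against 61 to 77% at 0.2 SD. This rests on the assumed R² of 0.10 to 0.40, independent covariates and simple randomisation. It applies where the covariate set matters: endline-only outcomes such as lipids, or an endline value analysed with covariates. By step 3 it hardly touches the linear group-by-time contrast.
- **By reasoning, not simulated:** for zinc deficiency under the logistic model, changing the covariates changes the conditional odds ratio that is estimated.
- **Conditional on the literal reading:** retained effects overstated by about 18 to 19% at 0.2 SD (1 to 17% for the interaction at the planned 0.27 SD), and dilution when the interaction is removed. The dilution figures come from 12 fits per scenario and show direction more than exact size.

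**What to change.** Delete the imbalance rule and the backward procedure, and put in their place, before the colour code is broken:

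1. One pre-specified model per outcome in which treatment terms always stay: group, time and group-by-time for repeated outcomes; group alone for endline-only outcomes such as lipids and red-cell fatty acids.
2. Adjustment in every model for the age-gender strata and the variables the randomisation was balanced on (serum zinc, BMI, zinc deficiency, HbA1c).
3. The baseline value of the outcome, where measured, used either as a response row or as a covariate, but not both. This applies equally when the outcome is itself one of the balancing variables.
4. A statement of whether this model or the ANOVA and chi-square tests are the primary analysis.
5. Each arm-versus-control estimate at six months reported with its 95% confidence interval, whether or not it is significant.

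The cost is text changes in the analysis section and the analysis plan. No further data or participants are needed.
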